### Outcomes {12}

All children who are screened and found to need further assessment and treatment (e.g. refractive services) will be given an appointment, approximately 1 week later, at a specified field ‘triage and treatment’ clinic or at a specialist ophthalmic hospital clinic. The primary outcome is attendance at this pre-specified appointment on the appointment date (yes/no).

The Peek software retains a record of every referred child. When children attend for these appointments, they are checked in using Peek software. This automatically updates their attendance status. Attendance data will be automatically reviewed by an algorithm every 24 h. The great advantage of the Peek-based screening programme is that is a closed data system with complete, unified data records for every person screened, their referral status and their attendance status. No additional data collection activities are required.*Primary outcome*: attendance at clinic on invited date. This is a binary outcome measure (yes/no). We will compare mean outcome rates between arms.*Secondary outcome*: days elapsed between appointment date and attendance. This is because children may miss their appointed day but attend at a later date. We will compare mean number of days elapsed between each arm.*Subgroup analyses*: attendance by age, sex, urban/rural residence, distance to clinic, ethnicity, guardianship, religion, language, household composition, migrant status, parental occupation, housing, assets and income.

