### Data collection and management

#### Plans for assessment and collection of outcomes {18a}

Referral status, attendance status and days elapsed since referral will be collected using the Peek Capture system on Android devices. Every time a participant is referred and every time they attend at clinic, they are checked in using an android device operating Peek Capture software. Additional data on sociodemographic characteristics will be collected when participants initially present to the screening programme.

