#### Data management {19}

Data will be collected by Peek’s implementing partners using Android devices through the Peek Capture application. Peek Capture enforces security controls that include strong device passcodes and native Android encryption. Data stored is time limited, the device syncs via an encrypted connection with a Peek-managed server, the data is then deleted to minimise the risk of data stored on the device.

Data will be stored on a Peek-managed server hosted in a Virtual Private Cloud (VPC) utilising the Amazon Web Services (AWS) Cloud. Each Peek-powered programme is hosted on its own dedicated server and a VPC that will reside in the UK/EU ensuring all of the data privacy safeguards as governed under the GDPR. All data collected is securely stored in AWS data centres which are state of the art, utilising innovative architectural and engineering approaches. Routine manual data cleaning will be conducted periodically by Peek administrators. Internal software guardrails will pick up simple errors.

Data collected can be monitored using Peek Admin; it tracks the Programme progress, provides insights and helps ensure no one is left behind. Data exported from Peek Admin will be pseudo-anonymised removing names and any other key identifiers, only the least amount of data will be shared, and where possible it will be fully anonymised and aggregated for research purposes.

At the analysis stage, data will be sent via a secure file transfer, using an encrypted zip file to LSHTM researchers to perform statistical testing. The zip file will be saved on the protected LSHTM server and only authorised named project staff will be given access. Passwords will be sent separately. Further details can be found in the Data Management Plan (Additional file 1: Appendix 2).

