#### Methods in analysis to handle protocol non-adherence and any statistical methods to handle missing data {20c}

The primary analysis only requires trial arm and the outcome (attendance) to be recorded. The trial arm should be recorded automatically as part of the Peek coding, and if it was missing it would be due to a bug in the coding. If this occurred, there is no statistical method that could be used to recover that data so any records with trial arm missing would not be included in the updating of the probability that an arm is best. We will check the code every 24 h to ensure that it is running as expected and correct any errors that we find immediately. The outcome cannot be missing, as a participant is set as ‘not attended’ until the point where they are updated as having ‘attended’.

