#### Composition of the data monitoring committee, its role and reporting structure {21a}

An independent Data and Safety Monitoring Board (DSMB) will be appointed by the trial steering committee. The DSMB will have three members, all independent of the running of the trial with relevant clinical and epidemiological experience.

The DSMB will confirm their specific meeting arrangements. It is proposed that the DSMB would meet prior to the beginning of the trial (Q2 2022), one third of the way through, and at the end, to assess the safety of the trial procedures. The DSMB will agree the way it will monitor the data, what it requires from the investigators in this respect and will communicate this to the PIs. All data can be interrogated remotely in real time.

The DSMB may visit the study coordination centre to assess data management, record keeping and other important activities. The DSMB will determine the manner in which it will monitor the data, what it requires from the investigators in this respect and will communicate this to the PIs.

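### A check-in that has not reached the server is scored as non-attendance in the daily update; the protocol treats this as proof that outcomes are never missing

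*Protocol article*

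**What the plan says.** Section {20c} states "The outcome cannot be missing, as a participant is set as" not attended until the record is changed to attended. Section {18a} says that when children are referred and when they attend, "they are checked in using an android device operating Peek Capture software". Data management {19} describes the next step: "Data stored is time limited, the device syncs via an encrypted connection with a Peek-managed server, the data is then deleted". The device and the server are therefore separate places, and a record moves from one to the other at sync.

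Outcomes {12} says "Attendance data will be automatically reviewed by an algorithm every 24 h". Sections {16a–c}, {20a} and {21b} use that daily reading to set the next day's allocation and to test whether one arm has a more than 95% probability of being best.

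Three statements point towards prompt and complete data. On check-in, Outcomes {12} says "This automatically updates their attendance status" and claims "complete, unified data records for every person screened". On monitoring, section {21a} says "All data can be interrogated remotely in real time".

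**The concern.** The outcome field is never empty, but it can be wrong. Once the appointment date has passed, a child still marked not attended may have stayed away, or may have attended with a check-in that has not been received. The default gives both the same value, so missing data become misclassified data.

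The error need not cancel between arms. Late sync would affect whole clinic-days, and the most recent ones. Those days contain more of whichever arm the algorithm currently favours. The voice arms join after six weeks, so all their early data are recent. A false run of failures can shift allocation or push the best-arm probability over its threshold. A late record is corrected at a later run, but the protocol describes no way to reopen a stopped trial, and allocations already made stay made. A record that is never received also reduces the measured effect.

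**Working it through.** **Inputs from the protocol.** About 160 referred children a day; attendance around 50%; appointment about one week after referral; daily review; more than 95% best-arm rule; voice arms after 6 weeks (6 × 5 = working day 30); a three-month limit, taken as 63–65 working days. The prior is stated through its 90% interval of 0.44 to 0.56. Beta(100,100) gives 0.442 to 0.558, which matches, so that prior was used.

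**Assumed, not in the protocol.** Four clinics a day (160 / 4 = 40 children per clinic-day), the share of clinic-days or records affected, and every sync delay.

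**Direct arithmetic.** Let *p* be the true attendance rate and *u* the share of attenders whose check-in has not been received.
- Scored rate = *p*(1 − *u*). At *p* = 0.50 this is 0.475, 0.45, 0.40 and 0.35 for *u* = 5%, 10%, 20% and 30%.
- With equal loss in both arms, scored difference = true difference × (1 − *u*). A 3-point effect with 10% lost reads 3 × 0.9 = 2.7 points; a 5-point effect with 20% lost reads 5 × 0.8 = 4.0.
- A new arm beside an old one: if only the newest daily cohort is affected, the new arm's first cohort is scored at 0.50(1 − *u*). An arm with 26 cohorts is scored at 0.50(1 − *u*/26). For *u* = 10% that is 0.45 against 0.498, although the true rates are identical.

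**Simulation of false best-arm stops.** Thompson sampling with identical arms at 50%, scoring only children whose appointment date had passed. The best-arm rule was applied daily, and whole clinic-days were late or lost. Ranges span repeated runs of 400 to 3,000 trials per scenario for two arms; the four-arm figures use 700 (error about 2 points).

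| Assumed sync pattern | Two arms | Four arms from day 30 |
|---|---|---|
| All records received | 37–39% | 30% |
| 10% of clinic-days 1 day late | 38–39% | 32% |
| 10%, 2 days late | – | 31% |
| 20%, 2 days late | about 52% | – |
| 10–20%, 5 days late | 44–86% | 35–72% |
| 10–20%, never synced | 46–62% | 42–55% |

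When unsynced clinic-days were held out of the update until received, the two-arm rate was 35–41%, that is, back at baseline.

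**Loss scattered over individual records instead of clinic-days** (four arms, 300 trials per scenario, error about 2 to 3 points). The rate was 30% with no loss, 24% with 10% of records one day late, 29% with 30% one day late, 83% with 30% three days late, and 25% with 30% never received. Scattered permanent loss falls equally on the arms and does not raise false stops. Loss of whole clinic-days can, because the arm mix changes from day to day.

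**The case against.** The strongest reply is that no late or failed sync is documented. The protocol describes automatic updating, complete records and real-time access, and it refers to a Data Management Plan (Appendix 2, not shown) that may fix the sync timing. Deletion from the device follows sync, so the time limit on device storage is no evidence of loss. Unblinded statisticians double-check the algorithm every 24 h and can stop the trial, the code is checked daily, and data are cleaned periodically. A clinic-day with no attendance against an expected 50% would be easy to notice. Late records also correct themselves.

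Much of this stands. It limits the size of the problem and rules out saying that nothing would prompt anyone to look. It does not close the gap. None of these statements says that every device has uploaded before each run. A check of the code can pass while a record is outstanding. A sync interval set elsewhere would not make the categorical sentence true.

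Some stronger readings are tempting but unsupported:
- That the trial will nearly always stop falsely. A rate of about 100%, with the worse arm named best in 18–23% of trials at a true 3-point difference (1–2% with complete data), appears only if the newest clinic-day misses every daily run throughout. Nothing in the protocol suggests that.
- That the 37–39% false-stop rate is due to this default. It is present with perfect syncing.
- That more clinics a day make the problem negligible. With ten clinics, 20% of clinic-days two days late gave 43%, and 20% five days late gave 84–86%.

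**Conclusion.** The point holds as a statement about the rule. As written, section {20c} turns non-receipt into non-attendance, and that value feeds allocation and stopping. How often this would happen cannot be derived from the protocol. On the assumed lags, occasional next-day delay has no detectable effect on stopping. Delays of several days, or clinic-days that never sync, can raise false stops well above baseline in both the two-arm and four-arm settings. Permanent loss also shrinks a true difference in proportion. These results assume that nobody notices or corrects the gap during the trial, which the planned daily checks make less likely for a clinic-day that is wholly absent. Priority is low to moderate.

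**What to change.** - Delete the statement that the outcome cannot be missing, and define three states: attended, not attended, and not yet known.
- Let a clinic-day enter the daily posterior only after its appointment date has passed and every device assigned to it has confirmed a sync. Until then its children are not yet known.
- Base the rule on sync confirmation, not on whether any check-ins were recorded. A clinic-day with confirmed sync and no check-ins is genuine non-attendance and must count; holding out empty days would select on the outcome.
- In the final analysis, report how many clinic-days were never confirmed, with the children affected by arm, and give a sensitivity analysis that includes and excludes them.

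The cost is one status flag in the data feed and one condition in the algorithm. Some outcomes enter the update a day or more later, so adaptation is slightly slower.

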#### Plans to give access to the full protocol, participant-level data and statistical code {31c}

The full protocol is available from the corresponding author. Statistical code will be made freely available online using GitHub. In line with the UK concordat on open research data (2016), anonymised participant-level data from this trial will be made available to bona fide research groups (evidenced via curriculum vitae and the involvement of a qualified statistician), and in line with the trial’s publicly available data sharing policy, following review and approval from the trial’s data monitoring committee. No reasonable request will be turned down, and the appropriate data will be made available within 1-month of receiving the request. There may be multiple levels of permission required in-country before data can be shared, including national ministry of health approval and local implementation partner approval.

### Patient and public involvement

Laypeople were involved in checking the wording of the intervention messages and suggesting refinements that better conveyed their underlying meaning.

#### Composition of the data monitoring committee, its role and reporting structure {21a}

An independent Data and Safety Monitoring Board (DSMB) will be appointed by the trial steering committee. The DSMB will have three members, all independent of the running of the trial with relevant clinical and epidemiological experience.

The DSMB will confirm their specific meeting arrangements. It is proposed that the DSMB would meet prior to the beginning of the trial (Q2 2022), one third of the way through, and at the end, to assess the safety of the trial procedures. The DSMB will agree the way it will monitor the data, what it requires from the investigators in this respect and will communicate this to the PIs. All data can be interrogated remotely in real time.

The DSMB may visit the study coordination centre to assess data management, record keeping and other important activities. The DSMB will determine the manner in which it will monitor the data, what it requires from the investigators in this respect and will communicate this to the PIs.

### Adverse event reporting and harms {22}

#### Definitions

**Table Tabb:** 

**Term**	**Definition**
Adverse event (AE)	Any untoward medical occurrence in a patient or study participant
Serious adverse event (SAE)	A serious event is any untoward medical occurrence that: Results in death Is life-threatening Requires inpatient hospitalisation or prolongation of existing hospitalisation Results in persistent or significant disability/incapacity Consists of a congenital anomaly or birth defect Other ‘important medical events’ may also be considered serious if they jeopardise the participant or require an intervention to prevent one of the above consequences.

#### Reporting procedures

All adverse events will be reported. Depending on the nature of the event the reporting procedures below will be followed. Any questions concerning adverse event reporting will be directed to the study coordination centre in the first instance. The flow chart below has been provided to aid the reporting of AEs.

#### Responsible personnel

##### Chief Investigator (CI)

The CI has overall responsibility for the conduct of the study and the ongoing safety and evaluation of any IMPs being used in the trial.Promptly notifying all investigators, Institutional Review Board (IRB) or Independent Ethics Committee (IEC) and Competent Authorities (CAs) of each concerned member state of any findings that may affect the health of the trial participants.Keeping detailed written reports of all AEs/ARs identified in the protocol as critical to the evaluation of safety within the agreed timeframes specified in the protocol.Accurate production and submission of the Development Safety Update Reports and progress reports to CAs and IRB/IECs.Collate all AR/AEs/SAEs/SARs and report to the Sponsor annually.Ensure that the PIs report all SAEs/SUSARs immediately to the Sponsor and to the CAs, IRB/IECs and any other relevant parties within agreed timelinesSupplying the Sponsor and IRB/IEC with any supplementary information they request.

##### Principal Investigators (PI)

The PIs have responsibility for the research performed at the local site, handling and management of investigational medical products, and informing the CI, Sponsor, Ethics, regulatory bodies and the trial coordinating team, of all adverse events that occur at their siteSafety responsibilities:Ensure trial participant safety and the swift and adequate management of trial participants with any type of AE/AR as per the management protocol described below.Reporting all SAEs/SUSARs immediately to the Sponsor and to the CAs, IRB/IECs and any other relevant parties within agreed timelines (i.e. LSHTM, EFMHACA, ORHB, FMOST).Assessing each event for causality, severity and expectedness. (Note: a medical decision which must be made by the investigator directly involved with the care of the patient/participant experiencing the AE)Ensure adequate archiving of AE records and reports in the local trial office along with the trial master files.Collate all AR/AEs/SAEs/SARs biannually and present to the CI.Guide and supervise the field research team on accurate recording, reporting of all adverse events.

##### Field Research Team Members (Coordinators, Nurses, Examiners, Recorders)

All field research team members are responsible for identifying, recording and reporting any AE or AR to the PIs regardless of severity or causality.Assessing each event for causality, severity and expectedness. (Note: a medical decision which must be made by the investigator directly involved with the care of the patient/participant experiencing the AE).Ensure that the participant has received the necessary management. This includes advice/reassuring, referral, offering transport, paying for management, making follow-up visitsReport to the PIs/Project manager AEs/ARs based on the specified timeline and file all AE/AR recorded forms in the trial master file.

##### Non-serious AEs

All non-serious AEs will be reported to the study coordination centre and recorded in a dedicated AE log within 72 h. The entry must state the patient ID, date and time of AE, nature and relation to the intervention, if any. The AE should also be reported to the data and safety monitoring committee within 72 h. AE logs will be stored on a secure, password-protected file on a LSHTM computer.

##### Serious AEs

Serious adverse events (SAEs) will be reported to the PI and study coordination centre within 24 h of the local site being made aware of the event. The PI will report the event to the data safety monitoring committee within 48 h and include it in the study safety report.

An SAE form will be completed and submitted to the PA and study coordination centre with details of the nature of event, date of onset, severity, corrective therapies given, outcome and causality. All SAEs whether expected, suspected or unexpected will be reported to regulatory bodies and the trial DSMB within 48 h of occurrence. The responsible investigator will assign the causality of the event. All investigators will be informed of all SAEs occurring throughout the study. If awaiting further details, a follow-up SAE report should be submitted promptly upon receipt of any outstanding information.

Any events relating to a pre-existing condition or any planned hospitalisations for elective treatment of a pre-existing condition will not need to be reported as SAEs.
[figure not shown]

Contact details for reporting SAEs

Please send SAE forms to: [contact] or [contact] using the title ‘SAE’

[contact] (Mon to Fri 09.00–17.00)

[contact]

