### Objectives {7}

Our objectives are to test a behavioural economics-informed SMS reminder message and a pre-recorded voice message that will be sent to the parents/guardians of school children who have been identified as having a visual impairment and referred to clinic. We hypothesise that these messages will be associated with a higher attendance rate than the current standard SMS reminder that is sent to all referred patients’ parents/guardians.

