### Eligibility criteria {10}

Reminder messages will be sent to the registered mobile phone numbers of parents/guardians of children who test positive at screening and are referred on to clinic in the Pono Yame MoH/Peek Vision school screening programme in 2022. Provision of a mobile number is a pre-condition of entry into the screening programme, although parents/guardians are able to supply the number of a friend or relative so in practice this stipulation does not exclude any children.

Reminders will be sent in English and Setswana; spoken by >96% of the local population. The screening programme routinely collects data on preferred language, and reminders will be sent in the preferred tongue. Those who list any language other than English of Setswana will receive the reminder in both Setswana and English. The reminder will also be sent in both languages to those where data on language is not available for any reason. We will perform a secondary analysis that excludes these participants, but they will be included in the primary analysis.

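### The SAE exemption for pre-existing conditions makes no exception for worsening of the referred eye problem, so a serious event of that kind has no clear route to the DSMB

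*Protocol article*

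**What the plan says.** The rule closing the Serious AEs section excuses two kinds of event from SAE reporting: "Any events relating to a pre-existing condition or any planned hospitalisations for elective treatment of a pre-existing condition". Earlier in the same section stands a general rule without qualification: "All SAEs whether expected, suspected or unexpected will be reported", to regulators and the DSMB, within 48 h.

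The population is described in Objectives {7} as "school children who have been identified as having a visual impairment and referred to clinic" and in Eligibility criteria {10} as "children who test positive at screening and are referred on to clinic".

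The table of definitions under Adverse event reporting and harms {22} lists, among the criteria that make an event serious, "Results in persistent or significant disability/incapacity".

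Three other sections deal with adverse events in general, and none contains the exemption:

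- Reporting procedures: "All adverse events will be reported".
- Field Research Team Members: staff are responsible for "identifying, recording and reporting any AE or AR to the PIs regardless of severity or causality".
- Non-serious AEs: these go to the coordination centre and a log, and to the data and safety monitoring committee, within 72 h.

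**The concern.** In many trials a clause of this kind keeps background illness out of the SAE listing. Here the background illness is the reason for entry. A reminder message can affect a child's eyes essentially only through whether and when the child attends, and these are the primary and secondary outcomes. Serious worsening of the referred problem after a missed or late appointment is therefore the event most closely tied to what is being tested, and the first limb excuses it from SAE reporting. An unrelated injury or infection that met a seriousness criterion would still be reported.

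What is at stake is the DSMB's view of safety. The committee is to assess the safety of the trial procedures and can stop the trial or suspend an arm, and participants are enrolled without individual consent. If eye-related SAEs may be left out, a report of no related SAEs is weak evidence that there were none.

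**Working it through.** The protocol gives no figure to reproduce here. The check is to follow one hypothetical event, serious worsening of the referred eye condition, through each reporting rule.

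1. **Is it an adverse event?** Yes. The definitions table counts any untoward medical occurrence in a participant.
2. **Can it be serious?** Yes, if it leads to lasting or significant disability. That is one of the listed criteria.
3. **Does the all-SAE rule capture it?** On its own wording, yes: every SAE, expected or not, goes to regulators and the DSMB within 48 h.
4. **Does the exemption remove it?** Read literally, it may. The two limbs are joined by *or*, so the first stands apart from the elective-admission limb. Worsening of a problem found at screening relates to a condition that existed before the message was sent. No exception is made for worsening or for the condition that led to referral.
5. **Do the general adverse-event rules bring it back?** In part. Field staff must still report it to the principal investigators. The Principal Investigators section has them inform the chief investigator, sponsor, ethics bodies, regulators and coordinating team of all adverse events at their site. The DSMB is not on that list.
6. **Does the adverse-event route to the committee cover it?** Not as worded. The 72 h route is written for non-serious events, and this event is serious.

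| Event | Route to the DSMB as written |
|---|---|
| Non-serious AE, any cause | Yes, 72 h |
| SAE unrelated to a pre-existing condition | Yes, 48 h |
| Serious worsening of the referred eye condition | Unclear: excused from the SAE route, outside the non-serious route |

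**Scale, for context only.** Sample size {14} expects about 160 referrals a day and the Background puts attendance at about 50%. That gives 160 × 0.5 = 80 children a day not attending. This counts non-attenders, not events. The documents give no rate of deterioration or vision loss, so no expected number of exempted SAEs can be calculated.

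**Could such events come to light?** In some children. Outcomes {12} anticipates attendance after the appointed date, and Methods for additional analyses {20b} expects about 10% of triage-clinic attenders to be referred on to hospital. Both are contacts at which worsening could be noted. No contact is described for a child who never attends.

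**The case against.** The strongest reply is that a general rule followed by a stated exception is not a contradiction, and that the exception touches only SAE classification. The general adverse-event duties remain, and the clause says such events need not be reported, which permits omission without forbidding a report. All of this is correct. It rules out the stronger reading, which a reader might infer, that vision loss after a missed appointment can never be reported, or that the DSMB is bound to see no eye-related SAEs. Vision loss from a new cause, such as an injury, is outside the clause. Nor is it shown that every child has a pre-existing condition in the strict sense, since entry rests on a positive screen and some referred children may have no confirmed diagnosis.

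A second reply is that the harm pathway is already watched. Attendance is reviewed every 24 h, unblinded statisticians check the algorithm's working, and the monitoring committee sees allocation and outcome data. A message that lowered attendance would show up directly. This also stands, but attendance is not the clinical event, and the SAE route exists to report the clinical event.

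Third, the interventions are described as negligible risk, and rewording the clause would not by itself find worsening in children who never attend. This limits the weight of the point.

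Finally, the adverse-event flow chart is not reproduced in the text available, and it may show a route for exempted events. If it does, the written sections should say the same.

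**Conclusion.** The point holds in a limited form. As worded, the exemption allows serious worsening of the referred eye condition to be left out of SAE reports to the DSMB. The event is still reportable to the principal investigators as an adverse event, but its route to the committee is unclear, and the exemption sits badly with the all-SAE rule in the same section. Essentially every participant's referred condition is within reach of the clause.

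This rests on a literal reading of the first limb and on the written sections without the flow chart. It does not depend on any count. A reader might multiply expected non-attenders by the share needing hospital assessment and take the product as the size of the problem. The documents do not support that: the 10% is for triage-clinic attenders, and the product would count children with an assumed specialist need, not serious events.

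The practical weight is modest. It is a cheap correction to safety oversight that the sponsor should make, and it does not threaten the trial's primary result.

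**What to change.** Keep the exemption for planned elective admissions. Add one sentence to the Serious AEs section along these lines: *The exemption for pre-existing conditions does not apply to worsening of the eye condition for which the child was referred, where that worsening meets a seriousness criterion in the definitions table; such events are reported as SAEs.*

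Then reconcile the Reporting procedures, Field Research Team Members, Non-serious AEs and Serious AEs sections, so that a site can see which rule governs such an event and how it reaches the DSMB. Check that the flow chart and the SAE form agree.

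The cost is a short protocol edit and a few additional SAE forms.
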